**Statistical Analysis**

Analysis will be by intention-to-treat using a repeated measures mixed modeling approach. Primary outcomes will be considered separately within each set (i.e., cognitive, wellbeing and productivity). Both univariate and multivariate analyses accounting for multiple comparisons and background variables will be conducted. Absence of any differences on primary outcome measures between ATO work location would lead to collapsing data across sites, otherwise SITE will be entered in the model as a covariate. For each analysis, within-subject change will be tested (TIME), followed by between GROUP differences, and then the main analysis will test the interaction between TIME X GROUP. Statistical significance will be set at alpha = 0.05. Treatment of missing values will depend on the extent and randomness of incomplete data.

Planned Subgroup analysis

A planned subgroup analysis of individuals categorized as high versus low on baseline cognitive testing (by median split of cognitive performance) will be conducted to determine if outcomes interact with initial level of cognitive competency.

Exploratory analysis

Depending on the nature of the results, exploratory structural equations modeling analyses may be run to determine the nature of any positive effects with respect to interactions between cognitive, wellbeing and productivity outcomes.

Power & Sample Size

Based on pilot study findings, effect size estimates for the domains of Memory and Executive function are presented in the table below. Note that positive effects are the desired direction for accuracy outcomes, and negative effects for response time outcomes. *Relative Effect Siz*e refers the Cohen’s d effect size in CCBT group (Pre-Post mean difference divided by pooled variance) minus the effect size in the control group.

|  |  | **Memory** | Executive Function |
| --- | --- | --- | --- |
| **Cohen's Relative Effect Size *d*** | **Accuracy** | 0.65 | 0.39 |
| **Response Time** | -0.51 | -0.99 |
| **Required Sample Size (n per group)** | **Accuracy** | 36 | 102 |
| **Response Time** | 66 | 22 |

Given the range of effect sizes observed, the most conservative effect size of 0.39 (on Executive accuracy scores) has been chosen. Controlling power at 0.8, 102 subjects would therefore be required per arm (rounded down to 100). After inflation for an expected 10% attrition rate, this results in an initial sample of N=220, (each arm to comprise n= 110).

References

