**Design**

A randomized, active controlled, single-blind, multi-centre intervention trial with longitudinal follow-up will be conducted. CONSORT criteria will be fully implemented in design and reporting. Subjects will be recruited, informed consent given, screened and then undergo a baseline set of assessments, followed by randomization (by computer generated sequence) to the CCBT arm or the active control arm on a 1:1 ratio. Subjectwise randomization will occur across all sites. Concealment of randomisation was achieved by central off-site administration and communicated via email. CCBT training will then commence for 16 weeks (4 months), followed by immediate proximal follow-up, and then longitudinal follow-up 6 months later (i.e., approximately one year since start of trial). The overall sequence of events is provided in **Figure 3**.

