**Outcome Measures**

As mentioned in Background, we will test CCBT rigorously against three ‘real-world’ sets of primary outcome variables. Background variables controlled for include age, gender and site. Outcome measures will be collected and supervised by a lead research organizational psychologist ([name]) who will remain blind to the training status of subjects.

1. Cognitive Capacities

Subjects will undergo a series of neuropsychological tests that will take no more than 1 hour, given the ATO’s preference to keep testing sessions brief. These will be administered in person by trained research psychologists and include:

1. Computer-based adaptation of WAIS-3 Matrix Reasoning 36: Form A and B will be counterbalanced at baseline and follow-up
2. A subset of tests taken from *Mindstreams*35*,* a validated computer-based neuropsychological assessment system: Verbal Memory, Non Verbal Memory, Staged Information Processing Speed, Visual-Spatial Orientation, Stroop Interference,
3. A subset of tests taken from *CogScreen*34,a validated computer-based neuropsychological assessment system: Visual Sequence Comparison, Divided Attention Parts I and II
4. Controlled Oral Word Association (COWAT): Form A (FAS) will be administered at baseline and Form B (CFL) at follow-up33

All tests each have alternate forms to minimize retest effects.

*Cognitive Primary Outcome Measures:* The following theory-based combinations of test outcomes will be calculated in the form of a sum of standardized z-scores to produce summary domain scores:

1. Memory: Verbal memory and Non-verbal memory
2. Attention: Divided attention Part I and Part II
3. Visual Spatial: Visual Spatial Orientation
4. Language: COWAT
5. Disinhibition: Stroop
6. Reasoning and problem solving: Matrix
7. Speed: Staged Information Processing Speed, Visual Sequence Comparison.

In addition, two *General Cognitive summary scores* will be calculated:

1. Average of domain scores
2. First principal component of baseline cognitive tests results

*Cognitive Secondary Outcome Measures:* Each individual cognitive test score.

2. Workplace Mental Wellbeing

We have operationalised workplace mental wellbeing to include 2 dimensions. Each is measured by a combination of internationally accepted and validated scale with known test-retest reliability and previous use in intervention trials.

1. Job Satisfaction:
   1. Overall job satisfaction scale 28 for positive appraisals

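### The 0.8 power is for one unadjusted test at 0.05, but the Protocol promises multiplicity-adjusted analyses of seven to nine cognitive primary outcomes and the sample size makes no allowance for that

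*Protocol*

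**What the plan says.** Outcome Measures sets up three "sets of primary outcome variables".

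- **Cognitive:** seven domain scores under the primary heading (memory, attention, visual spatial, language, disinhibition, reasoning and problem solving, speed). Two general scores follow before the secondary outcomes are introduced: the average of the domain scores and the "First principal component of baseline cognitive tests results".
- **Wellbeing:** two composites, job satisfaction and psychological wellbeing.
- **Productivity:** one composite.

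Statistical Analysis takes the primary outcomes set by set and states: "Both univariate and multivariate analyses accounting for multiple comparisons and background variables will be conducted". It then says: "Statistical significance will be set at alpha = 0.05". It names no adjustment procedure.

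Power & Sample Size uses one effect: "the most conservative effect size of 0.39 (on Executive accuracy scores) has been chosen". From that: "Controlling power at 0.8, 102 subjects would therefore be required per arm (rounded down to 100"). Attrition is then added: "After inflation for an expected 10% attrition rate, this results in an initial sample of N=220, (each arm to comprise n= 110"). Allocation is "to the CCBT arm or the active control arm on a 1:1 ratio".

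**The concern.** The primary outcome list, the promise of adjustment and the sample size are all fixed in the Protocol, and the third takes no account of the other two. A statistical analysis plan can name the adjustment procedure. It cannot make about 100 per arm deliver 0.8 for a given cognitive outcome once a familywise adjustment over seven or nine tests is applied.

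Two misreadings are at stake. If the adjustment is applied, a null result on a cognitive primary could be taken as coming from a trial with 80% power for it. If the adjustment is set aside to keep the stated power, each cognitive primary is tested at 0.05, and one isolated domain result could be presented as a primary success with no familywise control.

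**Working it through.** **Inputs from the Protocol.** d = 0.39, power 0.8, alpha 0.05, 102 per arm rounded down to 100, 110 per arm randomized, 10% attrition (110 × 0.90 = 99 evaluable), 1:1 allocation. Set sizes are m = 7 or 9 (cognitive), 2 (wellbeing) and 1 (productivity).

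**Assumptions.** The tests are two-sided, because sidedness is not stated and only this version comes close to the stated n. The comparison is a two-sample test on the standardized effect, as in the Protocol's own sizing. Adjustment is Bonferroni within a set.

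**Step 1: reproduce the plan's figure.** n per arm = 2(z₁₋α/₂ + z₀.₈)² / d² = 2(1.960 + 0.842)² / 0.39² = 103.2, or 104.2 by the t-test. The Protocol gives 102, within about two per arm. A one-sided test gives 82 and does not match. The stated n is therefore that of one unadjusted two-sided test.

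**Step 2: power at 100 per arm.** The noncentrality is 0.39 × √(100/2) = 2.758. The normal approximation is power ≈ Φ(2.758 − z₁₋α/₂ₘ). The t-test column is exact for a two-sample t-test.

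| Set | m | alpha/m | z | Power, normal | Power, t-test |
|---|---|---|---|---|---|
| Productivity | 1 | 0.0500 | 1.960 | 0.787 | 0.784 |
| Wellbeing | 2 | 0.0250 | 2.241 | 0.697 | 0.691 |
| Cognitive, domains only | 7 | 0.0071 | 2.690 | 0.527 | 0.517 |
| Cognitive, with general scores | 9 | 0.0056 | 2.773 | 0.494 | 0.483 |

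Šidák is almost the same as Bonferroni (0.497 for m = 9, normal approximation).

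**Step 3: other sample sizes (t-test).** At 99 per arm the cognitive figures are 0.511 (m = 7) and 0.478 (m = 9). With no attrition, at 110 per arm, they are 0.571 and 0.537.

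**Step 4: what would give 0.8 (t-test).** At 99 per arm, the detectable d is 0.507 (m = 7) or 0.519 (m = 9). For d = 0.39, about 166 (m = 7) or 174 (m = 9) evaluable per arm would be needed.

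**Step 5: sensitivity to the procedure.** These are simulated results for m = 9 at 100 per arm, with equal correlations between tests from 0 to 0.6. If one outcome alone has d = 0.39, power for it is 0.49 to 0.50 under Holm or Benjamini-Hochberg. If all nine have it, power for a given outcome is about 0.60 (Holm) or 0.73 to 0.75 (Benjamini-Hochberg).

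**The case against.** **No procedure is named.** This stands. A reader might infer that the plan simply has about half power. The documents do not support that as a fixed property: the figures of 0.48 and 0.52 belong to single-step familywise control, and a plan not shown here may choose otherwise. In the cases simulated for nine outcomes, however, no procedure reached 0.8 for a given outcome at d = 0.39.

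**The sentence also promises multivariate analyses.** This stands too. A joint test of the set at 0.05 needs no split of alpha. For seven domains at 99 per arm, a Hotelling test has power of about 0.90 if all have d = 0.39 and 0.57 if only one does, at an assumed inter-domain correlation of 0.3. At 0.5 it is 0.74 in both cases. The chance that at least one outcome is significant is also much higher than the chance for a named one. The figures above therefore concern one specified outcome.

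**The family is not twelve.** A reader might pool all the primaries (9 + 2 + 1 = 12) and quote a lower power and a pooled familywise error. The Protocol treats each set separately, so pooling contradicts its text. An unadjusted familywise error would also depend on correlations that the Protocol does not give.

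**Nine is an inference.** It rests on where the two general scores are listed. Placement favours nine, so both counts are shown.

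**Executive function.** A reader might infer that the planning effect is for a domain missing from the primary list. The Background section on population ageing equates problem solving with frontal-executive function, and reasoning and problem solving is a primary domain. That inference does not hold.

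**The planning effect is cautious.** It is the smallest in size of the four pilot effects. Under Bonferroni over nine at 99 per arm, power is 0.78 for an effect of size 0.51 and 0.96 for 0.65. This is fair context, but the stated 0.8 is for 0.39.

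**Conclusion.** The point holds within limits. The stated 0.8 describes one unadjusted two-sided comparison, and the sample size makes no allowance for the adjustment that the same section promises. Assuming Bonferroni within the cognitive set, two-sided tests and 100 evaluable per arm, power for d = 0.39 on one specified cognitive outcome is about 0.52 over seven or 0.48 over nine. Each wellbeing primary has about 0.69, and the single productivity primary is unaffected at 0.78. The shortfall is therefore mainly in the cognitive set and does not affect every primary in the trial. Its size depends on the procedure chosen and on how many outcomes respond.

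**What to change.** In Power & Sample Size, state that 0.8 applies to a single comparison at unadjusted two-sided 0.05. Name the adjustment assumed and restate the cognitive power at the adjusted alpha. Under Bonferroni that is about 0.48 over nine or 0.52 over seven, with a detectable d at 0.8 power of about 0.51 to 0.52 for 99 per arm. State also whether the two general scores count as primary, since that settles which figure applies.

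As an option, if the sponsor prefers to keep about 0.8 at 0.05, name one confirmatory cognitive primary, for example the average of the domain scores, and treat the other cognitive scores as multiplicity-controlled. This is a choice about endpoints, not a correction that the documents force. It also assumes that the effect of 0.39 carries over to the chosen score.

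Either change is a matter of wording and needs no more participants. The cost is a less favourable stated power in the first case, and single-domain claims that become secondary in the second.

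### The main TIME X GROUP test does not adjust for the pre-randomisation baseline, which costs precision, and no single follow-up contrast is named as the main test

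*Protocol*

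**What the plan says.** The Statistical Analysis section specifies an intention-to-treat repeated measures mixed model. For each outcome "within-subject change will be tested (TIME), followed by between GROUP differences, and then the main analysis will test the interaction between TIME X GROUP". The Outcome Measures section names age, gender and site as background variables to be controlled for; the baseline value of the outcome is not named.

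The Design section places the baseline assessment before randomisation. Training then lasts 16 weeks, "followed by immediate proximal follow-up, and then longitudinal follow-up 6 months later". Each outcome set is therefore measured three times, as the trial design figure also shows. No visit is named as primary, and the coding of TIME is not given.

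The Power & Sample Size text defines the planning effect as the trained arm's standardised change ("Pre-Post mean difference divided by pooled variance) minus the effect size in the control group"). It states that "the most conservative effect size of 0.39 (on Executive accuracy scores) has been chosen" and concludes: "Controlling power at 0.8, 102 subjects would therefore be required per arm (rounded down to 100". It mentions neither a within-subject correlation nor a third visit.

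**The concern.** Two features of the main test can be improved.

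- **Baseline.** Randomisation gives the two arms the same expected baseline mean. A model with TIME, GROUP and their interaction nevertheless estimates a separate baseline mean for each arm. The treatment effect at a follow-up visit is then a difference in change scores, and chance imbalance at baseline adds noise that an adjusted analysis would remove.
- **Target.** If TIME is a factor with three levels, the interaction is a joint test on 2 degrees of freedom. A significant result says that the arms differ at some follow-up, but not at which one. The sample size was set for one contrast.

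At stake are some power in a design with little to spare, and a clear reading of a positive result.

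**Working it through.** **Inputs from the protocol.** Effect 0.39; power 0.8; "Statistical significance will be set at alpha = 0.05"; allocation "to the CCBT arm or the active control arm on a 1:1 ratio"; 102 per arm rounded down to 100.

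**Assumptions.** A two-sided test (a one-sided test would need 82 per arm, so two-sided is what fits 102); equal variances at the visits; a baseline to follow-up correlation ρ, shown over a range because the protocol gives none.

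**1. The plan's own figure.** For one contrast on 1 degree of freedom, n per arm = 2(1.960 + 0.842)²/0.39² = 2 × 7.849/0.1521 = 103.2, so 104 (105 with the t distribution). The stated 102 agrees within rounding. At 100 per arm, power is 78.7%.

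**2. Variance with and without baseline adjustment.** With unit-variance scores, the per-arm factors for a baseline-to-follow-up contrast are:

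- baseline free in each arm (difference in change): 2(1−ρ)
- baseline as covariate, or a common baseline mean: 1−ρ²
- ratio: (1−ρ²)/[2(1−ρ)] = (1+ρ)/2

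**3. Effect on sample size and power.** The scale of the 0.39 is unclear. The text describes the divisor as "Pre-Post mean difference divided by pooled variance" and does not say whether it refers to raw scores or to changes, so both readings are shown.

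| ρ | Variance saved, (1−ρ)/2 | Change-SD units: n per arm for 80% power, planned → adjusted | Raw-SD units: n per arm for 80% power, planned → adjusted | Raw-SD units: power at 100 per arm, planned → adjusted |
|---|---|---|---|---|
| 0.3 | 35% | 104 → 68 | 145 → 94 | 64.5% → 82.4% |
| 0.5 | 25% | 104 → 78 | 104 → 78 | 78.7% → 89.0% |
| 0.7 | 15% | 104 → 88 | 62 → 53 | 94.5% → 97.1% |
| 0.8 | 10% | 104 → 93 | 42 → 38 | 99.2% → 99.6% |
| 0.9 | 5% | 104 → 99 | 21 → 20 | near 100% for both |

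Example at ρ = 0.3. In change-SD units, 103.2 × 0.65 = 67.1, so 68. In raw-SD units, the planned test needs 103.2 × 1.4 = 144.5, so 145; the adjusted test needs 103.2 × 0.91 = 93.9, so 94.

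**4. The interaction if TIME has three levels.** Take compound symmetry, ρ = 0.5, 100 per arm and raw-SD units. The two change contrasts have per-arm variance 1 and covariance 0.5. For effects (e₁, e₂) at the two follow-ups the noncentrality is (100/2) × (4/3) × (e₁² + e₂² − e₁e₂).

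| Effect at proximal, longitudinal follow-up | Noncentrality | Power, 2 df | Power, 2 df, common baseline mean |
|---|---|---|---|
| 0.39, 0.39 (persists) | 10.14 | 82.1% | 94.7% |
| 0.39, 0.195 (halves) | 7.605 | 69.4% | 83.3% |
| 0.39, 0 (vanishes) | 10.14 | 82.1% | 86.6% |

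The single baseline-to-proximal contrast with a free baseline has 78.7% power in the same setting. The formula is symmetric in e₁ and e₂, so an effect that vanishes (0.39, 0) and one that appears only later (0, 0.39) give the same noncentrality of 10.14.

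**The case against.** The strongest reply is that the planned analysis is sound, and that this point offers a better estimator without showing an error. Much of that stands. Several stronger readings are tempting, and the protocol does not support them.

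- **That the trial is powered for a different question.** The planning effect is itself a difference in pre-post change, which is the baseline-to-proximal component of TIME X GROUP. The sample size and the planned test treat baseline alike. Any mismatch comes only from a second follow-up entering the test.
- **That the test has 2 degrees of freedom and therefore loses power.** Three visits are stated, but a three-level TIME factor is an inference. Separate pre-post tests or a linear time term would have 1 degree of freedom, and an SAP that is not at hand may settle this. Even with 2 degrees of freedom, power is higher than for the single contrast in two of the three patterns above.
- **That planned power is only 64.5%.** That figure needs both raw-SD units and ρ = 0.3. In change-SD units the planned test needs 104 per arm whatever ρ is, close to the stated 102.
- **That the change contrast is always less precise.** The two analyses are equally precise when the regression slope on baseline is 1. With equal variances this happens only at ρ = 1.
- **That TIME or GROUP main effects would be taken as proof of benefit.** The protocol calls the interaction the main analysis and makes no such claim for the other two terms.

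It is also fair to say that any true interaction in a randomised trial reflects a real group difference at some follow-up, and that its direction can be read from the estimates. What the reply does not answer is that the protocol fixes the main test, does not list baseline among the controlled variables, and names no visit, although the better analysis uses data already being collected.

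**Conclusion.** The point holds as one of efficiency and of an unnamed target contrast. The planned test is valid and unbiased. Under equal variances it carries avoidable variance: 35% at ρ = 0.3, 25% at 0.5 and 15% at 0.7, and only 10% and 5% at 0.8 and 0.9. Since ρ is not in the protocol, the gain may be large or small. It deserves attention because there is little slack: 102 was rounded down to 100, and 110 per arm less 10% attrition leaves 99.

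The second part is conditional. If TIME is a three-level factor, power depends on how the effect evolves (about 82% or 69% at ρ = 0.5, under compound symmetry and raw-SD units), and a significant result does not show when the arms differ.

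**What to change.** Keep the mixed model and constrain the two arms to a common baseline mean, or enter the baseline score as a covariate. State that the main test is the 1-degree-of-freedom group contrast at proximal follow-up, which is the pre-post contrast the sample size was based on. Test the longitudinal follow-up contrast second.

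The cost is a change of wording in the Statistical Analysis section. Baseline is already collected for every outcome, so no added data, visits or participants are needed. The stated sample size can stay: with equal variances, adjustment can only reduce the number needed for this contrast.

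### SITE entered as a plain covariate cannot adjust the TIME x GROUP estimate, so the control for site that the protocol states does not reach the main analysis (nor would control for age and gender, if they enter the same way)

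*Protocol*

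**What the plan says.** Under Outcome Measures the protocol states: "Background variables controlled for include age, gender and site". Under Statistical Analysis it sets the model class: "Analysis will be by intention-to-treat using a repeated measures mixed modeling approach". It then adds: "Both univariate and multivariate analyses accounting for multiple comparisons and background variables will be conducted". Data are pooled over offices if the primary outcomes show no difference by location; "otherwise SITE will be entered in the model as a covariate". Of the effects tested, "the main analysis will test the interaction between TIME X GROUP".

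The Design section gives three assessments (baseline, end of the 16-week training, and six months later). Allocation is "to the CCBT arm or the active control arm on a 1:1 ratio", and "Subjectwise randomization will occur across all sites". No stratification is mentioned. The Sample section lists seven sites and an age range of 18 to 65.

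No interaction of a covariate with TIME is stated, nor any adjustment for the baseline score. The term by which age and gender enter is not given either.

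**The concern.** Site and gender do not vary over a subject's visits, and age is used as a background variable. Entered as a main effect, such a variable explains differences in level between subjects. TIME x GROUP asks only whether change differs between arms. The one adjustment term that the protocol spells out therefore acts on a part of the data that the main test does not use.

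What could matter for this test is a variable that predicts change: for example an office-wide shift in productivity during the trial, or practice gains that differ with age. If the arms happen to be unbalanced on such a variable, a main effect cannot correct for it. A reader of the results would nevertheless take the main comparison to be adjusted for site, and probably for age and gender. Making SITE unconditional would not help, because the form of the term is the problem.

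**Working it through.** **1. The protocol's own figure.** Inputs from Power & Sample Size and Statistical Analysis: d = 0.39, power 0.80, alpha 0.05 (two-sided assumed). n per arm = 2 × (1.960 + 0.842)² / 0.39² = 15.70 / 0.1521 = 103.2, that is 104, against 102 stated. This is close enough to count as reproduced. Power by the normal approximation is 0.795 at 102 per arm and 0.787 at 100. The calculation uses no covariates, so the point here does not touch the sample size.

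**2. Algebra.** For subject i at visit t, with group G and a time-constant covariate X:

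Y_it = b_t + g_t·G_i + c·X_i + e_it

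Y_it − Y_i0 = (b_t − b_0) + (g_t − g_0)·G_i + (e_it − e_i0)

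The term c·X_i has gone. The one remaining combination of a subject's visits that is uncorrelated with these differences carries its own free intercept and group parameter. It therefore tells us nothing about g_t − g_0. With complete data the TIME x GROUP estimate equals the unadjusted difference in change, whatever the covariance structure.

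The standard error is less protected. It is unchanged under compound symmetry and unstructured covariance. Under AR(1), variance parameters are shared across contrasts and get re-estimated when X is added.

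**3. Simulation** (110 per arm, 3 visits, 7 sites, random-intercept REML models, 25 data sets per scenario; variances and covariate effects are assumptions). Main-effect age, gender and site against no covariates, first follow-up:

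| Scenario | Change in estimate | Largest change in SE |
|---|---|---|
| Complete data | 0.000000 | 0.000001 |
| 10% attrition | mean about 0.001, largest about 0.02 | 0.0006 |

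The SE itself is about 0.12. In separate complete-data fits under AR(1) (three data sets, 100 per arm), the estimates were again identical, while the last-visit SE moved from 0.137 to 0.131, 0.147 to 0.141 and 0.146 to 0.137, a fall of about 4% to 6%. Another set of AR(1) fits gave 0.1% to 2%.

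**4. What TIME interactions would do.** Assume an age imbalance of 0.3 SD between arms and an effect of age on change of 0.2 per SD. The expected shift is 0.3 × 0.2 = 0.06. In simulation the mean estimate was 0.243 with no covariates, 0.243 with main effects and 0.309 with covariate x TIME terms, against a true value of 0.30. This is a large imbalance for chance: at 110 per arm its standard error is √(2/110) = 0.135 SD, so 0.3 SD is about 2.2 standard errors. It shows the mechanism and does not forecast this trial.

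**5. Precision.** Take 110 × 0.9 = 99 completers per arm and read 0.39 in SD units of the change score (assumption). Seven sites, age and gender give 6 + 1 + 1 = 8 parameters per follow-up visit. The efficiency factor is about 1 − 8/196 = 0.959, where 196 = 198 − 2. With R the share of change variance explained, power = Φ(0.39·√(0.959/(1 − R))·√(99/2) − 1.96):

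| R (assumed) | Power with TIME interactions |
|---|---|
| 0% | Φ(2.687 − 1.96) = 0.77 |
| 11% | Φ(2.849 − 1.96) = 0.81 |
| 20% | Φ(3.005 − 1.96) = 0.85 |

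Unadjusted power is Φ(2.744 − 1.96) = 0.78. Simulated values agree within about 0.01: 0.776 falling to 0.767 at R = 0%, and 0.82 to 0.845 for R = 11% to 20%.

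**The case against.** The strongest reply is that the protocol does not write the model being criticised. For age and gender it says only that they are controlled or accounted for. Covariate x TIME terms, or a multivariate model with a separate coefficient at each visit, would satisfy that wording and would not cancel. Such detail is commonly left to an analysis plan, which is not at hand. This stands for age and gender. A reader might infer that all three variables are known to cancel, but the documents do not support that. It stands less well for SITE: the protocol does name its form, and an analysis plan that followed that wording would carry the problem forward.

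A reader might also infer that nothing in the main test changes, p value included, under any covariance structure. That is too strong. The protocol names no structure, and under AR(1) the standard error does move.

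Finally, a reader might infer that the treatment estimate is biased or the test invalid. It is neither. Subjects are randomised, so the unadjusted TIME x GROUP test keeps its type I error, and chance imbalance is already reflected in its standard error. No figure in the documents shows that site or age predicts change. The gain from adjustment is therefore possible but unmeasured, and if there is none the fix costs a little power.

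**Conclusion.** The point holds in a limited form. SITE as a plain covariate leaves the TIME x GROUP estimate exactly unchanged with complete data and nearly unchanged with the planned 10% attrition. The control stated under Outcome Measures is therefore not delivered for site in the main analysis, and would not be for age and gender if they entered the same way.

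Validity and sample size are unaffected. The loss is adjustment for chance imbalance in predictors of change, plus possible precision. If these variables explained 11% to 20% of change variance, power would rise from about 0.78 to between 0.81 and 0.85; that share is an assumption with no source in the documents. This is a cheap improvement that makes the analysis do what the protocol says it does. It does not repair an invalid test.

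**What to change.** In Statistical Analysis, state in advance that SITE, age and gender enter the model with their TIME interactions (SITE x TIME, age x TIME, gender x TIME). An equivalent form would also serve, such as modelling the follow-up scores on the baseline score and these covariates. Reword the sentence under Outcome Measures so that it says the variables are controlled in that form.

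The cost is a sentence in each section and about 8 parameters per follow-up visit. If none of the variables predicts change, about 4% of efficiency is lost and power goes from about 0.78 to 0.76–0.77. No new data are needed and the sample size stays as it is.

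### The planned subgroup test cuts baseline cognition at the median, although continuous baseline scores are already planned and would give the interaction test more power

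*Protocol*

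**What the plan says.** In the Protocol, Statistical Analysis, Planned Subgroup analysis, the comparison is between "individuals categorized as high versus low on baseline cognitive testing (by median split of cognitive performance"). Its stated purpose is that it "will be conducted to determine if outcomes interact with initial level of cognitive competency". No analysis with a continuous moderator is mentioned for this question, no reason is given for a two-category cut, and no power is given for the interaction.

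Outcome Measures plans two general cognitive summaries, both continuous: "Average of domain scores" and "First principal component of baseline cognitive tests results".

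The sample size was set for the main comparison only: "the most conservative effect size of 0.39 (on Executive accuracy scores) has been chosen", and "Controlling power at 0.8, 102 subjects would therefore be required per arm (rounded down to 100"). The error rate is fixed by "Statistical significance will be set at alpha = 0.05". Under Design, subjects are randomised "to the CCBT arm or the active control arm on a 1:1 ratio".

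**The concern.** The question concerns a graded quantity: does the benefit of training change as baseline cognition rises? A median split treats everyone within a half as alike and treats two people just either side of the cut as different. If the true relation is smooth, that discards information.

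What is at stake is the power of the only planned subgroup analysis. The sample size calculation does not cover this test, so it has little power to spare. The method is fixed in the protocol itself, so an SAP that follows the protocol would carry it forward.

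There is a secondary hazard in display. The Statistical Analysis section tests within-subject change (TIME) before the TIME × GROUP interaction. If pre-post changes are shown by half for a cognitive outcome, regression to the mean alone will make the low half appear to gain and the high half to lose.

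**Working it through.** **Inputs from the protocol.** Effect size 0.39, power 0.8, alpha 0.05, 1:1 allocation, N = 220, attrition 10%.

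**Inputs assumed, because the protocol does not give them.** The shape of the baseline score, a linear interaction, its slope (SD of outcome per SD of baseline), and a baseline to follow-up correlation of 0.6. Tests are two-sided, and one follow-up is modelled.

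**1. The plan's own figure.** Two-sided, n per arm = 2(1.960 + 0.842)²/0.39² = 15.70/0.1521 = 103.2, or 104 with the t-distribution, against 102 stated. One-sided gives 82, so the plan is two-sided. Then 100 × 1.10 = 110 per arm gives N = 220. Completers are 220 × 0.90 = 198. There is no planned figure for the interaction to reproduce.

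**2. Information kept by the split.** For a linear interaction this is the squared correlation between the score and its high/low indicator. For a normal score it is 2/π = 0.637, a loss of 36.3%. The 198 completers then carry the information of 198 × 0.637 = 126 on the continuous score, and equal power would need 1/0.637 = 1.57 times as many people.

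| Assumed score shape | Information lost |
|---|---|
| Uniform | 25% |
| Normal with ceiling at +1 SD | 32% |
| Normal | 36% |
| Gamma, shape 4 (moderate skew) | 41% |
| t, 5 df | 46% |
| Laplace | 50% |
| Exponential | 52% |

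**3. Power for a cognitive outcome.** With correlation 0.6 the residual SD is √(1 − 0.36) = 0.8. The standard error of the interaction slope is 2 × 0.8/√198 = 0.114. At slope 0.3 the standardised effect is 0.3/0.1137 = 2.64 with the continuous score, and 2.64 × √0.637 = 2.11 with the split. Approximate power is Φ(2.64 − 1.96) = 0.75 and Φ(2.11 − 1.96) = 0.56. Simulation with the continuous baseline kept as a covariate in both models gives slightly lower values:

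| Assumed slope | Continuous moderator | Median split |
|---|---|---|
| 0.10 | 0.15 | 0.11 |
| 0.20 | 0.42 | 0.28 |
| 0.30 | 0.74 | 0.53 |
| 0.35 | 0.86 | 0.67 |

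A repeat simulation agreed with each entry to within 0.02. Analysing pre-post change instead leaves the continuous test unchanged, because baseline is already a regressor. It gives the split about 0.52 at slope 0.3 and 0.66 at slope 0.35. With a slope of zero, type I error was about 0.04 to 0.05 for every model.

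**4. Power for an outcome that baseline does not help predict.** With residual SD 1 and 200 completers, the formula gives continuous versus split power of 29% versus 20% at slope 0.2, 56% versus 39% at 0.3, 81% versus 62% at 0.4, and 94% versus 81% at 0.5.

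**5. The case that reverses the order.** If the effect jumps by 0.8 SD exactly at the sample median, the split has 80% power and the continuous test 60%.

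**6. Regression to the mean.** With correlation 0.6, no training effect in controls and a normal score, the expected change is −0.4 SD per SD of baseline. The mean of each half lies √(2/π) = 0.80 SD from the centre. The controls' expected change is therefore 0.4 × 0.80 = +0.32 SD in the low half and −0.32 SD in the high half. It is the same in expectation in both arms, so it cancels in the between-arm comparison.

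**The case against.** The strongest reply is that this is one subgroup analysis, not covered by the sample size calculation, and that the split gives a valid test. That stands: type I error holds, and nothing in the main analysis depends on it. For modest interactions the trial has little power either way (0.15 versus 0.11 at slope 0.1), so the change does not rescue the question. A slope of 0.3 beside a main effect of 0.39 would mean a training effect running from 0.09 to 0.69 SD across ±1 SD of baseline, and no document supports a value of that size.

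The figure of about a third also rests on normality and linearity, which the protocol does not state. That stands too, and is why a range is given.

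Three stronger readings are tempting and are not supported:

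- A reader might put split power as low as 0.44 at slope 0.3 and 0.56 at 0.35. Those values arise only if the split model also drops the continuous baseline. The protocol does not say it will, and its repeated-measures model uses the baseline measurement.
- A reader might infer that regression to the mean biases the subgroup test. It does not, because randomisation makes it equal in expectation in both arms. It distorts only within-half changes, and only on cognitive outcomes: wellbeing and productivity are not the variable being split.
- A reader might object that the cut depends on the sample. Sample percentiles, z-scores and a principal component do as well, so this does not separate the two methods.

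**Conclusion.** The point holds as one of efficiency. The protocol fixes a median split for a question about a graded moderator while planning continuous scores that would answer it better. Under a near-normal score and a linear interaction the split loses 36% of the information, and between 25% and 52% over the other shapes tried. At slopes of 0.2 to 0.35 that is about 14 to 21 percentage points of power for a cognitive outcome. The split would be preferable only if the effect stepped at the sample median, and the protocol gives no reason to expect that.

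The consequence is confined to the planned subgroup question. A reader should not infer that the subgroup test is invalid or that the main TIME × GROUP result or the sample size is affected. The absolute power figures depend on the assumed slopes and correlation and illustrate the size of the loss; they are not predictions for this trial.

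**What to change.** In Statistical Analysis, Planned Subgroup analysis, make the subgroup test the interaction GROUP × TIME × continuous baseline cognitive score. Name in advance one of the two general summary scores in Outcome Measures, for example the average of domain scores taken at baseline. Report the estimated training effect, with confidence intervals, at chosen percentiles of baseline such as the 25th and 75th. Keep the median split for descriptive display only, always showing both arms, so that within-half changes on cognitive outcomes are not read as training effects.

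The cost is a wording change in the protocol, and in the SAP if it repeats the split. No new data, participants or change to the main analysis are needed. The small downside is the linearity assumption, which a spline for the moderator can check as a sensitivity analysis.
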